### Sample size

A pilot study was conducted in November 2017 to inform sample size calculations. Pilot results are detailed in Supplementary Materials (see Additional file 3). Assuming a confirmed HBV and HCV testing response of 8.5% among intervention participants, 3.0% among control participants, a two-sided significance level of 5%, and 10% not evaluable (e.g., missing data), a total sample size of 674 men would be needed to have 80% power for an exact test. Power was calculated in SAS version 14.2 using the *twosamplefreq* statement in PROC POWER. The total sample size was rounded up to 700 for convenience, which corresponds to approximately 82% power under the above assumptions.

### Data collection and measures

Baseline and follow-up surveys will be delivered to mobile devices and completed online using Wenjuanxing (Sojump, Shanghai, China), a web-based survey tool that meets industry standards for security and functionality. Both surveys were written in Chinese, and 12 local MSM were asked to provide feedback to ensure questions are clear and culturally appropriate.

The baseline survey will first ask respondents to answer questions regarding eligibility criteria. If eligible, respondents will be asked to complete the remainder of the survey. The baseline survey will include the following domains: sociodemographic characteristics, sexual risk factors for viral hepatitis infection, previous HIV/STI testing behaviours and diagnoses, stigma toward people living with HBV, engagement in health promotion activities in the MSM community, access to primary healthcare services, access to MSM-competent healthcare, experiences with MSM stigma in healthcare settings, and trust in healthcare providers. Twenty-eight questions will measure sexual risk factors for viral hepatitis infection, which were adapted from the validated HCV-MOSAIC risk score for HCV infection among MSM [30]. Stigma toward people living with HBV will be assessed using the Toronto Chinese HBV Stigma Scale, a 20-item index validated for Chinese-speaking populations [12]. Engagement in health promotion activities will be measured through six items used in previous evaluations of crowdsourced interventions [31]. Access to MSM-competent healthcare will be assessed through three questions adapted from a recent survey investigating MSM-competent physicians in China [32]. Seven questions adapted from research in the United States will be used to measure experiences with MSM stigma in healthcare settings and trust in healthcare providers [33, 34].

Participants will receive a WeChat message 3 weeks after enrolment asking them to complete a follow-up survey within 1 week. The follow-up survey will collect information regarding the following self-reported outcomes: HBsAg and anti-HCV IgG test uptake, consultation with a specialist physician regarding HBV and HCV test results, HBV vaccination uptake, and HIV and STI test uptake since enrolment. Stigma toward people living with HBV will be reassessed. Participants will be asked to report their exposure to intervention materials and behaviours sharing intervention materials on social media during the four-week study period. Men in the intervention and control arms will receive the same follow-up survey. Men who have not completed the follow-up survey 2 days prior to the end of the four-week study period will be sent a reminder message. Both the baseline and follow-up surveys are expected to take less than 10 min to complete and are available in Supplementary Materials (see Additional file 4 and Additional file 5).

At any time after enrolment and throughout the four-week study period participants can submit photos of their HBV and HCV test reports through WeChat. Test report photos can also be uploaded along with the follow-up survey. The following information will be extracted and recorded from submitted photos: tester age, tester sex, date of test, and test result. No other personally identifiable information will be extracted. Mobile phone numbers and WeChat accounts will be used to link information extracted from test report photos to baseline and follow-up survey responses.

Among men assigned to the intervention arm, suggestions for improving crowdsourced images and videos will be collected through a web-based survey form hosted on Wenjuanxing. Information on contest participation will be linked to baseline and follow-up survey responses using mobile phone numbers and WeChat accounts.

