## Methods

### Trial design and timeline

This study will be an online superiority RCT. After completing a baseline survey to assess eligibility, enrolled participants will be randomly assigned in a 1:1 ratio into the intervention or control arms. Men randomly assigned to the intervention arm will be asked to view four crowdsourced images and videos promoting hepatitis testing over 8 days. After viewing each image or video men will be invited to submit suggestions for how to better tailor the crowdsourced materials to the MSM community. Men randomly assigned to the control arm will view no materials and will not be invited to submit suggestions. Participants can submit photos of hepatitis test reports to confirm HBV and HCV test uptake at any time after enrolment. After 3 weeks men will be sent a message asking them to complete a follow-up survey within 1 week. All participants will be assessed for primary and secondary outcomes at 4 weeks (28 days) post-enrolment (Table 1). The study is anticipated to begin enrolment in April 2018 and finish data collection by June 2018. A flowchart summarizing trial design and timeline is presented in Fig. 1.

**Table 1 Tab1:** Primary and secondary outcomes with definitions

Primary outcome	Definition
Confirmed HBV and HCV test uptake	Defined as men who had both HBsAg test uptake and anti-HCV IgG test uptake confirmed through electronic submission of a test report photo showing serology results, age of tester, sex of tester, and date of test within four weeks of enrolment
Secondary outcomes	
Confirmed HBV test uptake	Defined as men who had HBsAg test uptake confirmed through electronic submission of a test report photo showing serology results, age of tester, sex of tester, and date of test within four weeks of enrolment
Confirmed HCV test uptake	Defined as men who had anti-HCV IgG test uptake confirmed through electronic submission of a test report photo showing serology results, age of tester, sex of tester, and date of test within four weeks of enrolment
Self-reported HBV test uptake	Defined as men who had HBsAg uptake within four weeks of enrolment, self-reported in follow-up survey
Self-reported HCV test uptake	Defined as men who had anti-HCV IgG uptake within four weeks of enrolment, self-reported in follow-up survey
HBV vaccination uptake	Defined as men who had receipt of at least a one dose of the HBV vaccine within four weeks of enrolment, self-reported in follow-up survey

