HBV vaccination uptake among men with confirmed susceptibility to HBV infection	Defined as men with negative HBsAg and negative anti-HBs results confirmed through electronic submission of a test report photo showing serology results, who had receipt of at least one dose of the HBV vaccine within four weeks of enrolment, self-reported in follow-up survey
HIV test uptake	Defined as men who had HIV test uptake within four weeks of enrolment, self-reported in follow-up survey
Chlamydia test uptake	Defined as men who had chlamydia test uptake within four weeks of enrolment, self-reported in follow-up survey
Gonorrhoea test uptake	Defined as men who had gonorrhoea test uptake within four weeks of enrolment, self-reported in follow-up survey
Syphilis test uptake	Defined as men who had syphilis test uptake within four weeks of enrolment, self-reported in follow-up survey
Change in stigma toward people living with HBV	Continuous variable, defined as difference between Toronto Chinese HBV Stigma Scale score assessed at follow-up and baseline. Stigma toward people living with HBV will be measured at baseline and follow-up using 20 survey items that are each on a five point Likert scale. The 20 items were originally developed as the Toronto Chinese HBV Stigma Scale (potential range of 20–100), which has been previously validated and correlated to HBV testing behaviours among Chinese populations [39]. Decreased stigma toward people living with HBV will be defined as a mean composite score that is less at follow-up compared to baseline.
Visit with a physician after hepatitis test uptake	Defined as men who had HBV and/or HCV test uptake and saw a physician to discuss hepatitis test results within four weeks of enrolment, self-reported in follow-up survey

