#### Secondary analyses

The intervention and control arms will also be compared for differences in proportions of men achieving secondary outcomes, including confirmed HBsAg test uptake (independent of anti-HCV IgG test uptake), confirmed anti-HCV IgG test uptake (independent of HBsAg test uptake), self-reported HBsAg and anti-HCV IgG test uptake, HBV vaccination, and HIV and STI test uptake during the four-week study period. The analysis approach will be as described for the primary outcome. Change in stigma toward people living with HBV from baseline to week four will be calculated and compared between the intervention and control arms using a Wilcoxon ranksum test.

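### Self-reported secondary outcomes are defined over four weeks, but the only follow-up survey is answered between days 21 and 28, so up to a quarter of the window goes unobserved for early responders

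*Protocol article*

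**What the plan says.** Table 1 (under Trial design and timeline) gives the self-reported event outcomes a common window. For hepatitis B testing: "Defined as men who had HBsAg uptake within four weeks of enrolment, self-reported in follow-up survey". For HIV testing: "Defined as men who had HIV test uptake within four weeks of enrolment, self-reported in follow-up survey". The hepatitis C, chlamydia, gonorrhoea, syphilis and vaccination definitions follow the same pattern, and the physician-visit outcome requires that the man "saw a physician to discuss hepatitis test results within four weeks of enrolment, self-reported in follow-up survey". The design text fixes the assessment time for everything: "All participants will be assessed for primary and secondary outcomes at 4 weeks (28 days) post-enrolment".

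The survey timing is stated twice and consistently. The design section has "After 3 weeks men will be sent a message asking them to complete a follow-up survey within 1 week", and Data collection and measures has "Participants will receive a WeChat message 3 weeks after enrolment asking them to complete a follow-up survey within 1 week". The latter section describes the recall period as running from enrolment, for example "HBV vaccination uptake, and HIV and STI test uptake since enrolment". A reminder goes out two days before the four weeks end, but only to men who have not yet answered.

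Photos of test reports can be sent by WeChat throughout the four weeks or uploaded with the survey. Under Outcomes, a confirmed test must be dated within 28 days of enrolment. For stigma, Secondary analyses states: "Change in stigma toward people living with HBV from baseline to week four will be calculated".

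**The concern.** The outcome definition and the instrument do not match. A man can report only what has happened by the day he answers, and he is invited to answer from day 21. If he answers then and is tested, vaccinated or seen by a physician on day 25, the survey holds a completed no for an event that meets the Table 1 definition.

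Three consequences follow.

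- **Undercounting.** Self-reported uptake is too low, by an amount that varies from man to man with his response day. Because Secondary analyses applies the primary approach, a difference in proportions, equal proportional undercounting in both arms still shrinks the estimated effect.
- **No repair through the missing-data rules.** An early no is an observed value, so neither the complete-case rule nor multiple imputation touches it.
- **Mismatched measures.** A test on day 26 can be confirmed by photo in a man who has already reported no test. The Discussion presents photo confirmation as the answer to unreliable self-report, yet any comparison of the two measures would mix reporting error with a difference in window.

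Outcomes that need an earlier step, such as a physician visit after a test or vaccination in men shown to be susceptible, plausibly fall late and are the most exposed. The article gives no timing data to quantify this.

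**Working it through.** **Inputs, all from the protocol article.** The outcome window is 28 days (Table 1; Outcomes). The survey opens on day 21 and is to be completed within 7 days, so by day 28 (Trial design and timeline; Data collection and measures). The reminder falls on day 28 − 2 = 26 and goes to non-responders only.

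**Step 1: the plan's own sample size, to see whether it is involved.** The assumptions are 8.5% against 3.0%, two-sided 5%, an exact test and 10% not evaluable. Full enumeration of the two-sided Fisher exact test gives 80.03% power with 303 evaluable men per arm (606 in total), and 606/0.9 = 673.3, rounded up to an even 674. With 700 enrolled, 700 × 0.9 = 630 evaluable (315 per arm) give 81.8%. Both stated figures are reproduced. They rest on the photo-confirmed outcome, so the survey timing does not change them.

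**Step 2: unobserved share of the window.** Share = (28 − day of response)/28.

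| Day of response | Days unobserved | Share |
|---|---|---|
| 21 | 7 | 25.0% |
| 24 | 4 | 14.3% |
| 26 (reminder) | 2 | 7.1% |
| 28 | 0 | 0% |

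The range is 0% to 25%. If responses were spread evenly over days 21 to 28, the mean day would be 24.5 and the mean share 3.5/28 = 12.5%. That spread is an assumption.

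**Step 3: what this could do to a risk difference (illustration only).** The article gives no expected self-report rates, so I borrow 8.5% and 3.0% and assume that events occur evenly over the 28 days. Each observed rate is then the true rate × (day/28). Power is for the pooled z-test with 315 evaluable men per arm.

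| Response day | Intervention | Control | Difference (points) | Power |
|---|---|---|---|---|
| 28 | 8.5% | 3.0% | 5.5 | 84% |
| 24.5 (mean) | 7.4% | 2.6% | 4.8 | 79% |
| 21 (all men) | 6.4% | 2.25% | 4.1 | 72% |

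For the last row: 8.5 × 21/28 = 6.375 and 3.0 × 21/28 = 2.25, a difference of 4.125. The ratio between arms does not change; the difference does.

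**Step 4: which outcomes are reached.** The self-reported events are truncated. The confirmed composite and its two components are not, because WeChat submission stays open throughout the four weeks and eligibility turns on the test date. Stigma is a state on the day of the survey, so no events are lost. Its week-four label is merely loose for a score taken on days 21 to 28.

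**The case against.** The strongest reply is that little of weight is affected. The primary outcome and the sample size are untouched. Both arms receive the same survey on the same schedule, so the loss is not differential by design; a proportional loss leaves the ratio alone and pulls the difference towards zero, which is conservative for a superiority claim. The 25% is a ceiling. The materials are delivered over the first 8 days and reimbursement is announced at enrolment, so events may cluster early and fewer may fall in the last week than an even rate implies. The reminder also draws some answers to day 26 or later, where the loss is at most 7.1%.

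Most of this stands, and it limits the weight of the point. It does not remove the contradiction: the stated definition still cannot be measured in men who answer early, and a bias towards zero is still a bias in the estimate. Loss that differs by arm would require response speed to differ by arm, and the article gives no sign of that.

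A reader might go further and infer that the survey, by asking control men about hepatitis testing while a test can still count, dilutes the primary contrast. The article does not support that. Intervention men receive the same survey at the same time, and an equal additive prompt in both arms leaves a risk difference unchanged. Control men have also already met hepatitis questions at baseline and the reimbursement offer at enrolment. An effect is possible, but its size and direction are unknown. The survey wording itself is in an additional file that is not shown.

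**Conclusion.** The inconsistency is real and confined to the self-reported secondary outcomes. The definitions and the stated assessment time say 28 days, while the instrument covers 21 to 28 days depending on when each man answers. The unobserved share runs from 0% to 25% of the window per man. That range follows from the protocol's dates alone.

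Any average share, such as 12.5%, assumes evenly spread responses. Any statement about lost events or power also assumes an even event rate and borrowed uptake figures. It would be wrong to read the ceiling as saying that a quarter of self-reported events will be missed, or to extend the truncation to the photo-confirmed outcomes.

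This should be fixed before enrolment, because a no given early cannot be corrected afterwards from the survey data. It is not a threat to the primary analysis.

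**What to change.** Open the follow-up survey at day 28, word the event questions to cover exactly the 28 days since enrolment, keep it open for about one week, and move the reminder accordingly. Three matters of wording go with this:

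- State that only tests dated within 28 days count.
- State whether photos uploaded with the survey after day 28 are accepted for the confirmed outcomes, since the survey is also a photo route.
- Describe stigma as measured at the survey date.

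The cost is changed message dates and text, plus about one more week of data collection per man, to be checked against the planned June 2018 finish. The sample size stays as it is. The change also takes the survey contact out of the primary window.

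If the week-3 survey is kept, define the self-reported outcomes as events from enrolment to survey completion, record the completion date for each man, and stop calling them four-week outcomes in Table 1 and Secondary analyses. This costs almost nothing, but the window stays variable and still differs from that of the confirmed outcomes. Simply relabelling them as three-week outcomes would not be accurate: with recall running from enrolment, a man who answers on day 27 reports 27 days.

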### Confidentiality

Survey data will be collected through and stored on a secure online survey platform (Wenjuanxing). Photos of test reports will be collected through a secure online messaging platform (WeChat) or a secure online survey platform (Wenjuanxing). Participants will be instructed to cover or obscure their name and other personal identifying information on the test report to protect their privacy. Data will be transmitted using 128-bit encryption across the internet and mobile data networks. Responses to both baseline and follow-up surveys, including participant mobile phone numbers and WeChat account numbers, will be stored on a secure server which can be accessed with login information known only to the research team.

### Incentives and reimbursement

Participants who complete the initial survey will receive 4.73 USD (30 RMB), and those who complete the follow-up survey will receive an additional 7.89 USD (50 RMB). All testing costs up to 11.04 USD (70 RMB) for HBV and 6.31 USD (40 RMB) for HCV will be reimbursed to men who submit photos of their test results. Reimbursement amounts are based on prices of national standard HBV testing items (qualitative HBsAg, Anti-HBs, and Anti-HBc serological assay) and HCV testing items (qualitative anti-HCV IgG serological assay), respectively.

Men in the intervention arm who submit suggestions for improving hepatitis testing promotion materials will be eligible to receive contest prizes. Prizes of 78.88 USD (500 RMB), 31.55 USD (200 RMB), and 15.77 USD (100 RMB) will be distributed to one first-place finalist, two second-place finalists, and five third-place finalists, respectively. All incentives and reimbursements will be distributed as electronic money transfers through WeChat.

### Monitoring

A data monitoring committee will not be formed for this RCT because potential for harm to participants is minimal. If any person feels they have experienced an adverse event or unwanted effect from participating in this RCT, they can withdraw at any time. A telephone number and WeChat account will be provided to participants to contact the primary investigator with questions or concerns.

### Data analysis

#### Primary analysis

Participant baseline characteristics and outcomes will be summarized using descriptive statistics. The primary analysis will evaluate the hypothesis that the crowdsourced intervention is superior to control (i.e. no exposure) in increasing HBV and HCV testing among MSM in China. The proportion of men with confirmed HBsAg and anti-HCV IgG test uptake will be calculated for the intervention and control arms separately using a two-sided binomial 95% CI. The difference in proportions with test uptake will be calculated (intervention – control) with a corresponding Wald 95% CI. A Z-test will also be performed to compare the difference in proportions with test uptake between the intervention and control arms. If the 95% CI for the difference in probabilities is entirely above zero, then the intervention will be declared superior to control. If testing proportions are lower than anticipated such that statistical assumptions of the Wald CI are not met, then an exact 95% CI for the difference in probabilities will be used.

The effect of the intervention on HBV and HCV testing will first be evaluated using an intention to treat analysis that includes men lost to follow-up. Those who are lost to follow-up or do not respond will be counted as having not tested for HBV and HCV. An as-exposed analysis will also be performed that reassigns participants based on their self-reported exposure to the intervention materials and adjusts for potential confounders measured in the baseline survey.

#### Effect measure modification analysis

Effect measure modification analyses will evaluate whether the effect of the intervention on confirmed HBV and HCV testing varied in relation to the following factors measured at baseline: (1) engagement in health promotion activities in the MSM community, (2) access to primary healthcare services, (3) access to MSM-competent healthcare, (4) experiences with MSM stigma in healthcare settings, (5) trust in healthcare providers, and (6) age cohort (16–24 years old, 25–29 years old, and ≥ 30 years old). Age cohorts were selected based on previous epidemiological studies investigating HBV infection and vaccine-associated immunity among MSM in China [12].

#### Missing data plan

Any participants lost to follow-up will be included and assumed to have not achieved the primary and secondary outcomes during the study period. If an outcome is missing for < 15% of participants, analyses will use a complete-case approach. If an outcome is missing for ≥15% of participants, analyses will use multiple imputation.

#### Secondary analyses

The intervention and control arms will also be compared for differences in proportions of men achieving secondary outcomes, including confirmed HBsAg test uptake (independent of anti-HCV IgG test uptake), confirmed anti-HCV IgG test uptake (independent of HBsAg test uptake), self-reported HBsAg and anti-HCV IgG test uptake, HBV vaccination, and HIV and STI test uptake during the four-week study period. The analysis approach will be as described for the primary outcome. Change in stigma toward people living with HBV from baseline to week four will be calculated and compared between the intervention and control arms using a Wilcoxon ranksum test.

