**Methods:**

Seven hundred MSM will be recruited through social media operated by MSM organizations in China. Eligible participants will be born biologically male, age 16 years or older, report previous anal sex with another man, and reside in China. After completing a baseline online survey, participants will be randomly assigned to intervention or control arms with a 1:1 allocation ratio. The intervention will include two components: (1) a multimedia component will deliver two videos and two images promoting HBV and HCV testing developed through a crowdsourcing contest in China; (2) a participatory component will invite men to submit suggestions for how to improve crowdsourced videos and images. The control arm will not view any images or videos and will not be invited to submit suggestions. All participants will be offered reimbursement for HBV and HCV testing costs. The primary outcome is HBV and HCV test uptake confirmed through electronic submission of test report photos within four weeks of enrolment. Secondary outcomes include self-reported HBV and HCV test uptake, HBV vaccination uptake, and change in stigma toward people living with HBV after four weeks. Primary and secondary outcomes will be calculated using intention to treat and as-exposed analyses and compared using two-sided 95% confidence intervals.

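### Stigma (specific aim 2) is tested on raw change scores with no named between-arm estimate or interval; modelling the follow-up score on arm and baseline would supply both and usually add precision

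*Protocol article*

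**What the plan says.** Under Objectives, specific aim 2 and its hypothesis concern a greater reduction in stigma toward people living with HBV in the intervention arm. Table 1 describes the outcome as "Continuous variable, defined as difference between Toronto Chinese HBV Stigma Scale score assessed at follow-up and baseline", on a scale with a potential range of 20 to 100. It adds: "Stigma toward people living with HBV will be measured at baseline and follow-up using 20 survey items". It also states: "Decreased stigma toward people living with HBV will be defined as a mean composite score that is less at follow-up compared to baseline".

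The Secondary analyses section sends the differences in proportions to the primary-outcome approach, which gives a difference with a 95% CI. It then gives stigma its own method, in which the raw difference between the two surveys is to be "compared between the intervention and control arms using a Wilcoxon ranksum test". No effect estimate or interval follows.

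The abstract's Methods paragraph lists change in stigma among the secondary outcomes ("HBV vaccination uptake, and change in stigma toward people living with HBV after four weeks") and then says: "Primary and secondary outcomes will be calculated using intention to treat and as-exposed analyses and compared using two-sided 95% confidence intervals".

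**The concern.** Two things stand out.

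- **Reporting.** Aim 2 asks whether stigma falls more in one arm. The method named for it, as written, delivers a p-value. The abstract's undertaking to compare secondary outcomes by 95% CIs has no counterpart for stigma in the analysis section, so a reader would not learn from it how large the difference is or how well it is known.
- **Precision.** Every man completes the baseline survey, including the stigma scale, before randomisation, so the baseline score is available as a covariate at no cost. A change score forces its coefficient to 1. When the correlation between the two measurements is below 1, that coefficient is too large and baseline noise passes into the comparison.

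At stake are the precision and readability of a secondary aim for which the article states no power.

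**Working it through.** **Inputs from the documents.** 700 men, 1:1 allocation, 10% not evaluable (Sample size; Randomization and allocation). This gives 700 × 0.9 = 630 evaluable men, or 315 per arm. The stigma score is collected at baseline and follow-up (Table 1; Data collection and measures).

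**Inputs not in the documents.** No correlation, standard deviation, effect size or power is given for stigma, so there is no stated stigma figure to reproduce. The sample size statement (674 men for 80% power) concerns the primary outcome. It reproduces: Fisher exact power is 80.0% at 606 evaluable men, and 606/0.9 = 673.3, hence 674.

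**Variance.** Let the score have standard deviation s at both surveys and correlation r between them. Per man, the variance that enters the arm comparison is:

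- change score: 2s²(1 − r)
- ANCOVA: s²(1 − r²)
- ratio, ANCOVA to change: (1 − r²)/[2(1 − r)] = (1 + r)/2, which is below 1 for every r < 1

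The saving in men at equal precision is 1 minus the ratio. Where a change-score test has 80% power, ANCOVA has power Φ[(1.960 + 0.842)/√ratio − 1.960].

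| assumed r | change variance (s² = 1) | ANCOVA variance | ratio | fewer men needed | power where change score has 80% |
|---|---|---|---|---|---|
| 0.3 | 1.40 | 0.91 | 0.65 | 35% | 93.5% |
| 0.5 | 1.00 | 0.75 | 0.75 | 25% | 89.9% |
| 0.7 | 0.60 | 0.51 | 0.85 | 15% | 86.0% |
| 0.9 | 0.20 | 0.19 | 0.95 | 5% | 82.0% |

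**Simulation against the planned test.** 2,000 runs per setting, normal scores, 315 men per arm, and an assumed effect of 0.2 SD. The figures are power:

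| assumed r | Wilcoxon on change | ANCOVA |
|---|---|---|
| 0.3 | 54% | 76% |
| 0.5 | 70% | 82% |
| 0.7 | 88% | 94% |
| 0.8 | 98% | 99% |

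**Regression to the mean.** A chance baseline difference D between arms shifts the change-score comparison by (1 − r)D in the opposite direction. In SD units the standard error of D is √(2/315) = 0.080, so at r = 0.6 the typical shift is 0.4 × 0.080 = 0.03 SD. This is not a second, separate loss: 2(1 − r) − (1 − r²) = (1 − r)², so the excess variance of the change score is exactly the variance of this shift.

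**The case against.** The strongest reply is that nothing here is wrong. A rank-sum test on change controls type I error under randomisation. The endpoint is defined as a change and the hypothesis is about a reduction, so test, endpoint and hypothesis agree. All of that stands.

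Several stronger readings are tempting, and the documents do not support them:

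- *The baseline score is thrown away.* It is not. The change score subtracts it, but with a fixed rather than an estimated coefficient.
- *The abstract and the analysis section contradict each other.* They do not strictly conflict. Inverting the rank-sum test gives a Hodges-Lehmann shift with a 95% CI, and an unseen analysis plan may name it. What can be said is that the article names a method for stigma without one. That interval would be for a location shift, whereas Table 1 speaks of a mean score.
- *The trial will give no picture of how stigma changed.* The Primary analysis section promises descriptive summaries of outcomes. What is missing is a named between-arm estimate.
- *Multiple imputation is impossible with this test.* The narrower truth is that a rank-sum p-value has no estimate and standard error to pool by the usual rules. The Missing data plan calls for imputation only at 15% missing or more, and the sample size assumes 10% not evaluable, so imputation may never be needed.
- *The as-exposed analysis fails for stigma in particular.* The article names no adjustment model for any outcome, and the Z-test and Wald interval of the primary analysis take no covariates either.

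The reply is also right that the gain rests on an unstated correlation and on roughly normal scores. With skewed or heavy-tailed change scores, a rank test can match or beat a mean-based method.

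**Conclusion.** The point holds as an improvement in precision and reporting for a secondary aim. It does not show an invalid analysis. The article names no between-arm estimate or interval for stigma, although its abstract promises 95% CIs for secondary outcomes, and the comparison makes less than full use of a baseline score already in hand. The required number of men at equal precision falls by 35% at r = 0.3 and by 5% at r = 0.9, so the gain may be substantial or slight. That range assumes equal standard deviations at the two surveys and an r that the documents do not give; the power figures also assume roughly normal scores. The case for an estimate with an interval does not depend on r.

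**What to change.** State the main stigma analysis as a linear model of the follow-up Toronto Chinese HBV Stigma Scale score on randomised arm and baseline score, with robust standard errors, reporting the adjusted mean difference (intervention minus control) with a two-sided 95% CI. Keep the Wilcoxon rank-sum test on change as a sensitivity analysis, accompanied by the Hodges-Lehmann shift and its 95% CI.

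With baseline in the model, the arm coefficient is the same whether the follow-up score or the change is the response, so the Table 1 definition can stay. The same model permits standard pooling if the Missing data plan triggers multiple imputation. Baseline confounders can be added to it for the as-exposed analysis.

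The cost is wording in the analysis plan. No new data are needed, and the primary analysis and the sample size do not change.
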